## Background

In the 1960s, research started to demonstrate a strong relationship between physical inactivity and a variety of diseases and health conditions, including coronary heart disease, hypertension, obesity and osteoporosis. Several studies found that participation in regular aerobic exercise does in fact reduce the risk of suffering from such conditions[1–6]. With the increasing awareness of the benefits of physical activity, a more health conscious general population expressed interest in exercise. Recreational running, with its accessibility and low monetary cost, has grown increasingly popular among the general population as a primary form of exercise[7]. However, the increase in popularity of running has also led to an increase in running-related injuries. Previous retrospective and prospective running injury studies have found the yearly injury incidence proportion to range from 26-85%[8–13]. The effects of running injuries include short-term and long term pain and discomfort. Short-term pain and discomfort would be due to the immediate effects of the injury. Long term effects may include a reduction of physical activity, osteoarthritis following acute injury, and increased health care costs[14, 15]. This highlights the impetus for further investigation into running injury prevention, as this is a growing concern for the general population not only from a running injury perspective, but also from a health standpoint.

A variety of intrinsic risk factors that are inherent to the runner have been identified for running injury. Some of the most commonly studied intrinsic variables include muscle strength and joint kinematics and kinetics during running[16–18].

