### Sample size

Exploratory power analyses were completed for multiple biomechanical variables that will be tested in this study. Sample size was determined based on a sample size calculation using previously published data on the effects of balance training on the 95% ellipse area of the center of pressure as this was the largest reasonable sample size needed for the variables in this study[37]. It was found that in order to achieve 80% statistical power with an α = 0.05, 32 subjects would be needed to detect a change between training group and the control group with respect to the change in the 95% ellipse area following training with an effect size of 0.71. Assuming a 20% drop out rate, 40 subjects will be recruited for each of the groups in this project. Due to the sample size, the injury portion of this study will be a pilot RCT for developing a running injury prevention program. The information found in this study regarding the incidence of injury in each group will be critical for developing future RCTs investigating the impact of these interventions on running injury prevention.

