### Injury assessment

Participants will be asked to complete their allocated treatment two days per week before their running sessions for maintenance following the initial 8 weeks of training. The primary outcome measure for this portion of the research project will be running-related injuries. During the 6-month follow up period, running injuries will be tracked and documented for each participant using StudyTRAX, a web-based Electronic Data Capture system. Injuries will be identified using the “any physical complaint” definition as “any physical complaint developed in relation to running activities and causing restriction in running distance, speed, duration, or frequency”[70, 71]. Injuries reports will be completed weekly using the questionnaire that has previously been validated for overuse injuries[72]. An additional question will be added to this questionnaire asking the participant if they experienced any “physical complaint that prevented them from being fully able to participate in running activities”[72, 73]. If a participant answers “yes” to the final question, they will be contacted directly and asked to fill out the “time-loss” injury questionnaire using a “time-loss injury” questionnaire that was adapted for running injuries[74]. All “time-loss” injuries occurring during this time will be assessed by a physiotherapist. Injury incidence and severity for overuse injuries will be quantified by the average weekly incidence and severity scores from the overuse injury questionnaire[72]. Subjects will be asked to complete a physical activity log documenting their running routines as the number of minutes of running exposure on a weekly basis[42]. This will provide information regarding the running frequency per week as well as the length of time of each run in minutes. Due to funding limitations, heart rate monitors and GPS tracking were not available. Therefore, no information will be available regarding the type of run (tempo, steady state, intervals). Injury incidence and severity for acute injuries will be quantified by injury rate (number of injuries/1000 running hours) and the number of days taken away from running due to the injury[72]. Participants will also self-report their protocol adherence every week during the eight week intervention[75].

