Acute and overuse injury rates will be quantified separately due to the difference in injury definition[78]. Injury rates (number of injuries/1000 running hours) and 95% confidence intervals will be estimated. In an attempt to avoid the effects of dropout and adherence, an intent-to-treat analysis will be used. A multivariate Poisson regression analysis will be used to estimate incidence rate ratio (IRR) between the functional balance training group and the control group as well as between the isolated ankle strengthening group and the control group while controlling for age, gender and any other differences in baseline characteristics. Descriptive statistics for the amount of time missed from running due to injury (mean and standard deviation) will be calculated for both groups[79].

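### Injury rate ratios are planned with Poisson regression on counts not limited to first injuries, with no allowance for extra-Poisson variation; default intervals will be too narrow if runners differ in proneness

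*Protocol article*

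**What the plan says.** The Analysis section of the protocol article names one model for injuries: "A multivariate Poisson regression analysis will be used to estimate incidence rate ratio (IRR) between the functional balance training group and the control group", and likewise for isolated ankle strengthening against control. It adjusts for age, gender and other baseline differences. The quantity reported is set out as "Injury rates (number of injuries/1000 running hours) and 95% confidence intervals will be estimated". The same section adds: "Acute and overuse injury rates will be quantified separately due to the difference in injury definition".

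Injury assessment describes the data: "During the 6-month follow up period, running injuries will be tracked and documented for each participant". On frequency it says: "Injuries reports will be completed weekly using the questionnaire that has previously been validated for overuse injuries". Running time is logged per person, "documenting their running routines as the number of minutes of running exposure on a weekly basis". No sentence restricts counting to the first injury, and none mentions overdispersion, a robust variance or a negative binomial model.

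Under Sample size, the article states that "the injury portion of this study will be a pilot RCT for developing a running injury prevention program".

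**The concern.** Poisson regression with default standard errors takes the variance of each runner's count to equal its mean, given covariates and exposure. If some runners are inherently more prone to injury, counts spread more widely than that. The estimated rate ratio is still aimed at the right quantity, but its standard error is too small.

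The trial's own argument makes unequal proneness plausible. The Background section attributes injury risk to muscle strength, joint movements and joint moments. Such factors enter the injury model only if they happen to differ between the groups at baseline. A factor that is balanced across arms but varies among runners stays out of the model and still adds variance.

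The article calls the injury information critical for developing later trials. Intervals that are too narrow would carry false precision into that planning, and could make a training arm look protective by chance.

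**Working it through.** **The plan's own figure.** The article gives no rate, dispersion or power for injuries. Its only sample-size calculation concerns the 95% ellipse area: n = 2 × (1.96 + 0.84)² / 0.71² ≈ 31.1, so 32 per group, and 32 / 0.8 = 40. This reproduces the stated numbers but does not bear on the injury analysis. It supplies only the 40 per arm used below.

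**Scale of the counts.** The Background section cites a "yearly injury incidence proportion to range from 26-85" percent. Assuming a constant, common rate, the mean over 6 months is μ = −ln(1 − p) / 2:
- p = 0.26: −ln(0.74) / 2 = 0.15
- p = 0.85: −ln(0.15) / 2 = 0.95

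This only sets a scale. With unequal proneness, the same proportion would imply a higher mean.

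**Assumption.** Between-runner variance k (gamma-distributed proneness with mean 1) is not in the documents. I take k = 0, 0.5, 1 and 2.

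**Large-sample formula.** The count variance is μ(1 + kμ), so the dispersion is φ = 1 + kμ. The true standard error of the log rate ratio is √φ times the default one. The actual error of a nominal 5% Wald test is 2 × [1 − Φ(1.96 / √φ)]. For μ = 0.5 and k = 1: φ = 1.5, √φ = 1.225, error = 11.0%.

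**Simulation.** Two arms of 40, no true effect, running hours varying with a coefficient of variation of 0.3, unadjusted log rate ratio, 20,000 runs per setting. Each cell shows error with the default Poisson variance, then with the sandwich variance:

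| μ | k = 0 | k = 0.5 | k = 1 | k = 2 |
|---|---|---|---|---|
| 0.15 | 2.4 / 2.6% | 3.1 / 3.0% | 3.6 / 3.1% | 4.7 / 3.5% |
| 0.3 | 4.2 / 4.5% | 6.1 / 5.2% | 7.7 / 5.4% | 10.9 / 6.0% |
| 0.5 | 4.6 / 5.0% | 7.4 / 5.1% | 10.7 / 5.7% | 16.3 / 6.1% |
| 0.95 | 4.5 / 5.0% | 11.0 / 5.8% | 16.6 / 6.3% | 25.8 / 6.6% |

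The formula gives, for k = 0.5 / 1 / 2:
- μ = 0.3: 6.8 / 8.6 / 12.1%
- μ = 0.5: 8.0 / 11.0 / 16.6%
- μ = 0.95: 10.7 / 16.0 / 25.0%

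From μ = 0.3 upward, formula and simulation agree within about 1.5 percentage points. At μ = 0.15 the formula overstates the error, because there are too few events for the large-sample approximation.

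**Size on the standard error.** At k = 1, √φ runs from √1.15 = 1.07 (μ = 0.15) to √1.95 = 1.40 (μ = 0.95).

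**What drives it.** In the k = 0 column, runners can be injured repeatedly and the error never exceeds 5%. Unequal proneness is the cause, not recurrence.

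**Effect of splitting by injury type.** If a mean of 0.95 were split evenly (an assumption) into 0.475 each, then at k = 1 φ = 1.475 and the error is 10.7%, against 16.0% for the combined count.

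**The case against.** The strongest reply is that this is a condensed article. It fixes the model family, effect measure, contrasts and covariates. The variance estimator and any dispersion check are commonly left to an analysis plan, which is not shown. A sandwich variance is compatible with the article's wording, and the article does not say that default standard errors will be used. That stands as a limit on the claim. It does not remove the point, because Poisson regression is the one method stated and a better version of it costs almost nothing.

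A reader might infer that the intervals will be too narrow and false positives too frequent, simply because runners can be injured more than once. The documents do not support that:
- They give no injury rate for the trial, no dispersion and no rule for counting recurrences.
- At a mean of 0.15 there is no inflation even with k = 2.
- If only first injuries were counted, without person-time, the Poisson test would be conservative (simulated error 0.2–1.5%).

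Three further points reduce the size:
- Acute and overuse injuries are analysed separately.
- Adjustment for age, gender and baseline differences may absorb some heterogeneity; the simulation is unadjusted.
- Injury assessment attaches the rate per 1000 running hours to acute injuries and summarises overuse injuries by average weekly scores. The weekly overuse questionnaire is therefore weak evidence that many repeat counts enter the Poisson model.

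Finally, the injury part is a declared pilot and did not drive the sample size, so a false positive carries less weight than in a confirmatory trial.

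**Conclusion.** The point holds conditionally. The named model makes no stated allowance for extra-Poisson variation in counts that may exceed one per runner. If proneness varies beyond the adjusted covariates, default intervals are too narrow.

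For k between 0.5 and 2, the type I error of a nominal 5% test is about 3–5% at a mean of 0.15, 6–11% at 0.3, 8–17% at 0.5 and 11–26% at 0.95. These figures rest on the assumed k, on 40 analysed runners per arm, on no covariate adjustment and on all injuries being counted together. Separate acute and overuse analyses would sit lower in that range.

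It would go too far to call inflation certain or the defect critical. The rate ratio estimate is not biased by overdispersion, the data needed are already collected, and the injury part is a pilot. It should be fixed before the analysis.

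**What to change.** Keep both contrasts against control and the same covariates, with log running hours as offset. Fit either Poisson regression with a robust (sandwich) variance at runner level, or negative binomial regression. Take the 95% confidence intervals for the group rates from that same model. It would help to state alongside this whether recurrences count as new injuries, since that decides how far the problem applies.

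The cost is a line of text and a software option. Running minutes are already logged, so no new data are needed. Intervals become somewhat wider where runners differ, and little is lost where they do not. In the simulation the sandwich variance kept the error between about 3% and 7%, so slight inflation can remain at 40 per arm when heterogeneity is strong.

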## Methods/Design

### Study design

This is a randomized controlled trial (RCT). In total, 120 novice runners will be recruited. Subjects will be randomly assigned to one of three groups: an isolated ankle strengthening group (n = 40), a functional balance training group (n = 40) or an activity matched control group (n = 40). The study design and flow can be seen in Figure 1. Research ethics approval was obtained from the University of Calgary’s Conjoint Health Research Ethics Board (Ethics ID: REB13-0153).

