### Randomization procedure

In order to protect against selection bias, subjects will be randomly assigned to one of the three groups. The generation of an unpredictable randomized allocation sequence will be completed using randomization.com through the use of a random allocation scheme (one block, size 120) with a 1:1:1 allocation ratio between the three groups. This randomization procedure was chosen to avoid selection bias with predictable random assignments using smaller block sizes in a non-blinded study design. This task will be completed by an individual that is not involved in the trial. In order to ensure allocation concealment, sequentially numbered, opaque, sealed envelopes (SNOSE) will be used. Once potential subjects have provided written, informed consent, they will sequentially draw an envelope and write their details on that envelope before opening to determine their group allocation. All envelopes will be similar in appearance and weight and cardboard will be placed within the envelope in order to make it impermeable to light.

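### Time missed through injury is to be summarised for two unnamed groups in a three-arm trial, by a plain mean and SD that cannot flag lay-offs still open at last contact

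*Protocol article*

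**What the plan says.** The Study design section has three arms: "Subjects will be randomly assigned to one of three groups", with 40 runners in each. The Randomization procedure section confirms this ("one block, size 120) with a 1:1:1 allocation ratio between the three groups").

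The Injury assessment section sets the observation window: "During the 6-month follow up period, running injuries will be tracked and documented for each participant". It measures the severity of acute injuries by "the number of days taken away from running due to the injury". Overuse injuries are handled separately: "Injury incidence and severity for overuse injuries will be quantified by the average weekly incidence and severity scores from the overuse injury questionnaire".

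The injury paragraph of the Analysis section plans a Poisson model with two contrasts, balance against control and strength against control, so that model uses all three arms. The next sentence fixes the severity summary: "Descriptive statistics for the amount of time missed from running due to injury (mean and standard deviation) will be calculated for both groups". It is not restricted to acute injuries.

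On dropout, the same paragraph says only that the analysis will follow intention to treat. The Sample size section assumes 20% dropout and describes the injury part as a pilot that will inform later trials.

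**The concern.** There are two problems, and both lie in what the sentence fixes.

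**Number of groups.** The word *both* refers to two groups, but three are randomised. Followed literally, one arm would have no summary of time missed, and the reader cannot tell which. If the two training arms are meant, the control arm, which is the comparator in every hypothesis, would have no figure.

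**Choice of statistic.** Follow-up stops at 6 months, and some runners will leave earlier. A runner who has not yet resumed running at that point has a lay-off known only to exceed the days seen so far. A plain mean and SD has no place for that information. Entering the observed days as if complete pulls the mean down, and pulls it furthest for the longest lay-offs. Intention to treat keeps runners in their assigned arm but does not complete an unfinished lay-off.

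What is at stake is a descriptive severity figure that later trials may use for planning. If that figure is too low and carries no count of unresolved injuries, its users cannot see the problem.

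**Working it through.** **1. The article's own design figure.** The only design calculation is the sample size, for the 95% ellipse area: effect size 0.71, α = 0.05 (two-sided assumed), power 80%.

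- n per group = 2 × (1.960 + 0.842)² / 0.71² = 31.1, rounded up to 32.
- With 20% dropout: 32 / 0.80 = 40.

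Both stated figures reproduce. Neither concerns time missed, so the point leaves them untouched.

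**2. Group count.**

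| Place | Groups |
|---|---|
| Study design; Randomization procedure | three, 1:1:1 |
| Analysis, Poisson model | three, in two contrasts with control |
| Analysis, time missed | *both*, not named |

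The third row cannot be reconciled with the first two.

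**3. Shortfall in the mean for a fixed lay-off.** Assumptions, none of them from the article: a 6-month window of T = 182 days, injury onset uniform over the window, a lay-off of length L ≤ T, and open lay-offs entered at observed length.

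- Share still open at T: L/T.
- Mean recorded length: L − L²/(2T).
- Relative shortfall: L/(2T).

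| L (days) | Share open | Mean recorded (days) | Shortfall |
|---|---|---|---|
| 30 | 30/182 = 16% | 30 − 900/364 = 27.5 | 8% |
| 60 | 60/182 = 33% | 60 − 3600/364 = 50.1 | 16% |
| 90 | 90/182 = 49% | 90 − 8100/364 = 67.7 | 25% |

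Onset concentrated early in follow-up would make these shortfalls smaller.

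**4. Skewed lay-offs, with and without withdrawal.** A simulation used the same window and uniform onset, lognormal durations with log-SD 1.0 and 1.3, and either no withdrawal or 20% exponential withdrawal unrelated to injury. Each range below spans the two log-SDs.

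| Assumed median (days) | Recorded/true mean, no withdrawal | Recorded/true mean, 20% withdrawal | Share open, 20% withdrawal |
|---|---|---|---|
| 14 | 69–84% | 68–83% | 13–17% |
| 28 | 54–71% | 53–70% | 25–29% |
| 56 | 39–55% | 38–53% | 43–44% |

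The end of follow-up produces nearly all of the shortfall; withdrawal unrelated to injury adds one or two percentage points. The simulation does not cover runners who leave because of their injury.

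**5. Likely number of injured runners.** The Background cites yearly injury proportions of 26% to 85%. Assuming a constant hazard, the 6-month proportion is 1 − √(1 − p): 1 − √0.74 = 14% and 1 − √0.15 = 61%. Of 40 runners, that is about 6 to 25 per arm.

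**The case against.** The strongest reply has four parts.

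**No arm is shown to be left out.** A reader might infer that one arm will have no severity data. The article does not support that: it names no omitted arm, the sentence just before uses all three, and *both* may be a slip or may mean the two training groups. This stands. The defect is a contradictory and ambiguous sentence.

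**Nothing says open lay-offs are counted as complete.** A reader might also infer that the plan records the worst injuries as mild ones. No sentence says so, and a rule for injuries open at last contact is the kind of detail an article leaves to the full protocol or analysis plan. This stands as well, so the absence of a rule is not the point here, and the understatement is conditional. What remains is that the article has already chosen the statistic, and that statistic cannot carry the information however such a rule is worded elsewhere.

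**The consequence is limited.** The primary outcome of this part is running-related injuries, and the inferential analysis is the rate ratio. Time missed is descriptive, in a pilot, and overuse severity also has its own questionnaire score. The 6-month cutoff is common to all arms, and nothing in the article suggests that injured runners would leave more often from one of them. All of this stands and keeps the point modest.

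**The sizes are assumed.** The article gives no lay-off durations, and its 20% dropout was set for a sample size based on a measure taken within 9 weeks, so carrying it to 6 months is a further assumption. This stands. It also rules out claiming that ordinary dropout makes the loss much larger, since the simulation shows almost no change. A mean is, moreover, a legitimate measure of total time lost and should be kept alongside the additions.

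**Conclusion.** The point holds in a limited form. The group count is contradicted outright: two unnamed groups against three randomised arms. This needs no assumption and must be corrected.

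The second part is conditional. If lay-offs open at 6 months or at withdrawal are entered at observed length, the mean is too low. The direction is certain under that condition. The size depends wholly on durations the article does not give: 8%, 16% and 25% for fixed lay-offs of 30, 60 and 90 days with uniform onset over 182 days, and more if durations are strongly skewed. A difference in bias between arms would need injury-related withdrawal to differ by arm, for which there is no evidence in the article.

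The effect is confined to a descriptive severity measure in the pilot injury part. The incidence rate ratio, the hypothesis tests and the sample size do not change.

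**What to change.** Change the sentence on time missed as follows:

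- Replace *both groups* with *each of the three groups*.
- Among injured runners, report median and IQR of days missed alongside mean and SD.
- As the burden measure, report mean days lost per runner followed, counting uninjured runners as zero. A per-runner median would be zero wherever fewer than half the runners are injured, which covers most of the 14–61% range above. This mean also stops counting at last contact, so it should be read with the next item.
- Report by arm the number of lay-offs unresolved at 6 months or at withdrawal, and the number of runners who stopped running because of injury.
- Summarise time to return to running by Kaplan-Meier, censoring unresolved lay-offs, and note that censoring at withdrawal may be informative because runners may leave on account of the injury.

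The cost is wording and a small table, with no new visits. Weekly reports run through follow-up, but the article does not describe the content of the time-loss questionnaire, so the sponsor should confirm that onset and return dates are captured. The drawback is imprecise Kaplan-Meier estimates if injuries per arm are few; the unresolved count and the median remain useful even then.
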